# Dance-based avenues to advance nonpharmacologic treatment of chemotherapy effects (DAANCE): Study protocol for a multi-center, randomized controlled trial

**DOI:** 10.21203/rs.3.rs-6814353/v1

**Published:** 2025-07-07

**Keywords:** chemotherapy-induced neuropathy, oncology, neurorehabilitation, music, dance, biomechanics

## Abstract

**Background:**

Breast cancer (BC) is among the most common forms of cancer, particularly among women. Chemotherapies that are most effective in treating BC are known to cause chemotherapy-induced neuropathy (CIN), thus leaving survivors with sensory deficits including pain, numbness, and tingling in the extremities; functional deficits such as impaired neuromotor control and motor-cognitive integration; reduced quality of life; and increased fall risk. Current pharmacologic treatments show limited efficacy and create additional unwanted side effects. In contrast, physical activity (PA) has emerged as a promising nonpharmacologic candidate for managing CIN symptoms. The purpose of this trial is to evaluate the effect of Adapted Argentine Tango (Tango) as a potential treatment for CIN. Toward this end, we will assess the intervention effect of Tango vs. the standard of care (SOC) on patient-reported outcomes of sensation, clinically-relevant measures of function, and potential mechanisms of action. We hypothesize that 4 weeks of Tango practice will improve sensation and function more than SOC among BC survivors with CIN and demonstrated balance dysfunction.

**Methods:**

In a multi-center, prospective, randomized controlled clinical trial, participants are randomly assigned (1:1 ratio) to the Tango experimental or the SOC active control arms. Primary outcomes are measured from baseline to after 4 weeks of intervention in patient-reported outcomes (PROs) of sensation and dual-task function. Secondary outcomes include additional PROs, such as fatigue, and clinical measures of interest after 4 and 8 weeks of intervention and 1 month following intervention completion. Exploratory measures include postural control, gait stability, cognitive load, and blood-based biomarker concentrations. Linear mixed models will be used to model changes in PROs and function. The primary estimand will be the difference in mean change in primary outcomes from baseline to week 4 between treatment groups.

**Discussion:**

The scientific premise of this study is that Tango stands to improve CIN symptoms significantly more than the current standard of care by combining PA with auditory-motor entrainment and social engagement. Our findings may lead to a safe non-pharmacologic intervention that improves CIN-related deficits.

**Trial registration:**

This trial was first posted on 12/27/24 at ClinicalTrials.gov under the identifier NCT06749210.

## Introduction

### Background and rationale

Breast cancer (BC) is one of the most diagnosed cancers, with an estimated 2.3 million diagnoses in 2020 that disproportionately affected women (1). Of those that receive a BC diagnosis, it is estimated that 64.5% will undergo chemotherapy treatments with taxane-based agents (2) that cause secondary conditions that complicate aging, such as chemotherapy-induced neuropathy (CIN) (3–9). Up to 80% of breast cancer survivors who undergo chemotherapy develop CIN (4, 8). The manifestation of CIN may cause delay or discontinuation of life-saving chemotherapy treatment and decrease quality of life (8, 10). Symptoms include disabling pain, numbness, tingling, and/or burning in their hands and feet (6, 11, 12); a decrease in neuromotor control (13–16); deficits in motor-cognitive integration (17); and increased fall risk (18, 19). At present, treatment options for CIN are limited (6). Despite extensive research, no pharmacologic intervention has significantly improved the neuromotor, functional, and patient-reported symptoms of chronic CIN among BC survivors. Instead, pharmacologic interventions focus on managing symptom development through nerve pain relief (e.g. gabapentin) or serotonin reuptake inhibitors (e.g. duloxetine). However, these pharmacologic solutions come with side effects, such as drowsiness and suicidal ideology. Therefore, there is a critical need to address the neurosensory motor symptoms of neuropathy created through chemotherapy treatments among BC survivors.

Physical activity (PA) is a promising nonpharmacologic candidate in the treatment of CIN (20–25). Possible training effects of PA include reduced systemic inflammation (26), axonal regeneration in the peripheral nervous system (27), and improved executive function (28). However, additional research is needed for progressive and prescriptive exercises relevant to the resolution and/or reduction of CIN as well as to understand adherence to a program. Social dance has been proposed as a candidate PA to promote adherence (29). Social dance can be delivered as progressively challenging PA (30) that addresses functional targets of CIN such as balance and motor-cognitive integration (17, 31–33), and promotes intrinsic motivation and adherence over conventional exercise programs (17, 29, 31, 34).

Among potential social dance forms, Adapted Argentine Tango (Tango) has been used to improve motor and cognitive impairments in Parkinson’s Disease (32), another population that experiences neuropathy and increased fall risk. As a partnered dance, Tango is a form of PA with potential to active the human dynamic system via rhythmic entrainment (17, 29, 35), has been associated with better intrinsic motivation to participate than traditional exercise programs (29), and may serve as rehabilitation for postural control (36–38), gait function (36, 39), and patient-reported outcomes of symptoms similar to those reported by BC survivors with CIN (40–42). Further, pilot data show the feasibility of Tango as a potential PA-based solution for cancer survivors with CIN symptoms (17, 29, 38).

We hypothesize that Tango will improve CIN compared to usual care. To evaluate this hypothesis, we will evaluate the effect of Tango, a light to moderate intensity social dance adapted for persons with mobility deficits (30, 32) and breast cancer survivors (17), on patient-reported symptoms of chronic CIN, function with respect to motor-cognitive integration, and potential physiological mediators of sensation and function among BC survivors. Research by the multiple principal investigators (MPIs) established Tango as feasible for aging survivors (up to 82 years old) to engage in biweekly at a dose of 33(4) (mean(SD)) min/session with high satisfaction and positive effects (32, 38) and specifically efficacious for motor-cognitive integration in doses of approximately 20 min/class (17). We hypothesize that Tango will improve sensation, dual-task function, and their potential physiological mediators among BC survivors who demonstrate CIN with balance dysfunction.

### Objectives

The primary objective of this experiment is to rigorously evaluate Tango as a nonpharmacologic intervention for neuropathy symptom relief – including patient-reported numbness and tingling (Aim 1 primary outcome) and dual-task function (Aim 2 primary outcome) - and to establish the first exploratory data regarding mechanisms supporting positive effects, such as change in brain activity, biomechanics, and blood-based biomarkers. We hypothesize that 4 weeks of Tango practice (2x/week; 15–30 min dose of movement-to-music per session) will improve sensation (Aim 1) and dual-task function (Aim 2) more than usual care among BC survivors with CIN and demonstrated balance dysfunction; we further hypothesize that exploratory measures will show change with 8 weeks of Tango practice.

## Methods

### Study Design

This is a multi-center, prospective randomized controlled study of superiority between an experimental intervention and usual care control arm. Eligible participants who provide informed consent will be randomly assigned to the Tango experimental (EXP) or the standard of care (SOC) control group (CON) in a 1:1 ratio. The study primary endpoints are changes from baseline to 4 weeks of intervention in the patient-reported outcome (PRO) of the sensations of numbness and/or tingling (Aim 1) and the quantitative outcome of dual task function during performance of a cognitive challenge simultaneously with a walking task (Aim 2). As an exploratory endpoint, we will assess the effect of Tango on the blood-based biomarkers that potentially mediate sensation and function as well as on cognitive load during a dual-task paradigm as measured by brain activity (i.e. high gamma) (Aim 3). Tables 1 & 2 present the data collection schedule for the EXP and CON groups, formatted per the Standard Protocol Items: Recommendations for Interventions Trials (SPIRIT) recommendations (43–45). Figure 1 illustrates the overall study design as a flow diagram. As detailed in Tables 1 & 2, outcomes are assessed at the following timepoints: repeated baseline (Baseline), primary endpoint (4 weeks of intervention or SOC), 8 weeks of intervention, 12 weeks (follow-up after a 4-week period of no structured intervention being offered), and weekly for 6 months following intervention end. Secondary outcome measures include clinical and biomechanical tests of function and patient-reported outcomes that complement the primary outcome measures in addition to falls incidence. Tertiary outcome measures, listed in Table 3, include within-session effects, satisfaction collected at session end, and surveys used to inform monitoring and shaping of interventions including Rating of Perceived Exertion - Physical (RPE-P; 6–20 scale), Rating of Perceived Exertion - Mental (RPE-M; 6–20 scale), and Intrinsic Motivation Inventory (IMI). To support beneficence, individuals randomized to the control arm will be given the option of participating in the experimental intervention after primary outcomes measurement.

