#### Cognitive load

Brain activity will be collected via electroencephalography (EEG) and occur at baseline, after 4 weeks of SOC or INT, and after 8 weeks of intervention. EEG data collection will occur in the same facilities mentioned in the *Study Setting* section, using a mobile EEG system (eego, ANT Neuro, Netherlands) with 24-channels (waveguard net, ANT Neuro, Netherlands), sampling at a frequency of 2048 Hz. EEG signal processing and analysis will follow Crasta et al. (2018) (115) using BV Analyzer (Brain Vision LLC, Garner, NC) to extract mean activity per frequency band, phase synchrony, and event-related potentials.

The protocol to assess cognitive load follows that of [name] et el., 2024 (17). EEG signals were collected during the performance of the following postural and motor-cognitive tasks. Conditions listed in Table 4 below are completed by each participant while standing with their shoes off, feet 7 cm apart from the inside of their feet, hands to their side, and facing comfortably straight ahead. Participants will be guarded by trained research staff during standing tasks and will get a break at the halfway mark of each task. Each task lasts for 3 minutes. Auditory stimuli will be presented through ER-3A-inserted earphones (Etymotic Research, Elk Grove Village, IL) via a custom-made program in PsychoPy (Open Science Tools, Nottingham, England).

For the visual and auditory oddball, each stimulus is presented for 500 ms with a random inter-stimulus interval from 500 ms to 1 second. A total of 100 stimuli are presented (80 standard and 20 oddball).

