### Statistical analysis

All outcome analyses will be performed on an intent-to-treat basis, and all hypothesis tests will be two-sided and at the 5% significance level or 95% confidence level. Longitudinal linear mixed models will be used to model changes in PROs and dual-task function. Fixed effects will be included for condition, session number within condition, baseline outcome measure, age, diabetes status, physical fitness activity (defined by weekly duration and metabolic equivalents), and number of previous chemotherapy lines. Random effects for subjects and study center will be used to account for within-subject and within-center correlation, and covariance estimated by restricted maximum likelihood. Exploratory Aim 3 will be assessed via causal mediation analysis using marginal structural models. The primary estimand will be the contrast representing the difference in mean change in outcome measure from baseline to week 4 (end of randomized treatment comparison) between treatment groups.

While we expect balance between groups due to randomization, we will adjust for potential confounders including age, body mass index, concurrent medications, and other variables if an imbalance between groups occurs by chance. Pearson’s *R* will be calculated to correlate PROs, functional outcomes, biomechanical outcomes, brain activity, and biomarker outcomes. We use a longitudinal mixed effect model to analyze all outcomes and do not impute missing outcomes. Subjects will be analyzed in the group to which they were randomized regardless of compliance with the assigned intervention. We will evaluate the effect of the number of intervention sessions completed on outcomes.

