## Figures and Tables

**Figure 1 F1:**
[figure not shown]
Flow chart of study design from screening through the follow-up (f/u) period with assessments indicated throughout. Postural control data will be taken at each Tango session in addition to all assessment periods. Each assessment timepoint may contain 1) clinical measures: PROs, dual-task function, and upper extremity function; 2) biomechanical measures: postural control and gait stability; and 3) exploratory measures: biomarker and EEG sampling. For more detailed information, refer to tables 1 & 2. Processing of data will happen after the conclusion of the follow-up period per participant. Analysis of the primary outcome measures will be conducted after all data has been collected.

**Table 1 T1:** SPIRIT report of intervention effect outcome measures for EXP group.

	Study Period						
	Enrollment		Allocation	Post-Allocation			
Timepoints	3 + months post-last taxane exposure	Baseline	0	EXP 4 weeks (Tango midpoint)	EXP 8 weeks (Tango end)	EXP 12 weeks (1-month follow up)	6-month follow up period, assessed weekly
ENROLLMENT:							
Eligibility screen	x						
Informed consent	x						
Allocation			x				
ASSESSMENTS:							
Adverse events (including falls)		x^†^		x	x	x	x
Neuropathy (primary outcome Aim 1)		x^†^		x	x	x	x
TUG-Cog (primary outcome Aim 2)		x		x	x	x	
CTCAE		x^†^		x	x	x	
Pain		x^†^		x	x	x	
Fatigue		x^†^		x	x	x	
GAD-2		x		x	x	x	
PHQ-2		x		x	x	x	
SF-36		x		x	x	x	
Satisfaction with intervention				x	x		
Activity outside of study tracking		x^†^		x	x	x	x
Intrinsic motivation				x	x		
Postural control during silence (QEC)		x^†^		x	x	x	
Postural control during music listening (QECm)		x^†^		x	x	x	
TUG		x		x	x	x	
TNSr+		x		x	x	x	
MiniBEST		x			x		
6mwt (EMG, IMUs)		x			x		
Upper extremity function		x		x	x	x	
Goal attainment (COPM)		x			x	x	
Blood-based biomarkers		x			x		
Cognitive load (EEG)		x		x	x	x	

† indicates a measure was repeated 3 times

**Table 2 T2:** SPIRIT report of intervention effect outcome measures for CON group.

	Study Period							
	Enrollment		Allocation	Post-Allocation				
Timepoints	3 + months post-last taxane exposure	Baseline	0	CON 4 weeks (post-SOC)	CON 8 weeks (Tango midpoint)	CON 12 weeks (Tango end)	CON 16 weeks (1-month follow up)	6-month follow-up period, assessed weekly
ENROLLMENT:								
Eligibility screen	x							
Informed consent	x							
Allocation			x					
ASSESSMENTS:								
Adverse events (including falls)		x^†^		x	x	x	x	x

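### The first EEG after baseline coincides with the week-4 primary outcomes, so causal mediation through EEG (exploratory Aim 3) cannot be identified within the randomised period

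*Protocol article*

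**What the plan says.** In the protocol article, Study Design places two things under Aim 3: the effect of Tango on blood biomarkers, and its effect on EEG ("as well as on cognitive load during a dual-task paradigm as measured by brain activity (i.e. high gamma) (Aim 3"). Objectives lists brain activity among the mechanisms of interest: "mechanisms supporting positive effects, such as change in brain activity, biomechanics, and blood-based biomarkers". Statistical analysis then states, with no exception for EEG: "Exploratory Aim 3 will be assessed via causal mediation analysis using marginal structural models".

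On timing, the Cognitive load section says EEG recordings "occur at baseline, after 4 weeks of SOC or INT, and after 8 weeks of intervention". Tables 1 and 2 agree that the first EEG after baseline is at week 4 in both arms, and Table 3 lists no EEG within sessions. Study Design fixes the primary outcomes at that same time: "The study primary endpoints are changes from baseline to 4 weeks of intervention". Statistical analysis calls week 4 the end of the randomised comparison. The section on the control intervention lets controls move to Tango directly after the week-4 assessments.

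**The concern.** Causal mediation needs a mediator that comes before the outcome. Here the only EEG after baseline in the randomised period is taken at the outcome timepoint. Less numbness or easier standing could itself alter EEG, most of which Table 4 has recorded while standing. A same-timepoint mediation model fits that situation as well as it fits EEG change driving the improvement. Marginal structural models adjust for measured confounders; they do not decide which of two simultaneous measurements came first.

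At stake is the mechanistic conclusion. Part of Tango's effect could be credited to brain activity that only tracks the benefit. The primary analyses are not touched.

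**Working it through.** **1. Schedule, from Tables 1 and 2**

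| | EXP | CON |
|---|---|---|
| EEG | baseline, weeks 4, 8, 12 | baseline, weeks 4, 8, 12, 16 |
| TUG-Cog | baseline, weeks 4, 8, 12 | baseline, weeks 4, 8, 12, 16 |
| Numbness/tingling | same visits, plus each Tango session (Table 3) | same visits, plus weekly during SOC (Table 3) |
| Tango received by week 4 | 4 weeks | none |
| Tango received by week 8 | 8 weeks | 4 weeks, if crossed over |

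EEG and TUG-Cog share every scheduled timepoint. Symptoms are recorded between baseline and week 4, but EEG is not. The symptom item also looks back 7 days (Primary outcome measures, Sensation), so the week-4 score partly describes days before the week-4 EEG. No EEG after baseline precedes either primary outcome within the randomised window.

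**2. Lagged pairings.** Week-4 EEG with a week-8 outcome is ordered in time. By week 8, however, a control who crossed over has had 4 weeks of Tango and EXP has had 8. The contrast is then no longer Tango against SOC as randomised.

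**3. The plan's own power figures.** The article gives no power for Aim 3. For the primary outcomes, with 50 per arm and two-sided 5%:
- Aim 1: pooled SD = √((2.5² + 1.9²)/2) = √4.93 = 2.220. Standardised difference = 1.25/2.220 = 0.563. Power is 80.4% (normal) or 79.6% (t).
- Aim 2: d = 0.56. Power is 80.0% (normal) or 79.2% (t).

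Both match the stated 80%, so d = 0.56 and 50 per arm are fair inputs for an illustration.

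**4. Illustrative worst case.** Let EEG be purely a consequence of the outcome:
- Outcome: Y = 0.56·T + e, with var(e) = 1.
- EEG: M = r·Y + √(1 − r²)·u, with var(u) = 1. EEG has no effect on Y.

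Fit M on T, then Y on T and M:
- Path T to M: a = 0.56·r.
- Path M to Y given T: b = r, the within-arm slope, since both variances are 1.
- Apparent indirect effect: a·b = 0.56·r².
- Apparent mediated share: 0.56·r²/0.56 = r². The true share is 0.

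| Assumed r | a·b | Share r² | Simulated share | Both paths significant at 5% |
|---|---|---|---|---|
| 0 | 0 | 0% | 0% | 0.3% |
| 0.3 | 0.0504 | 9% | 9% | 11% |
| 0.5 | 0.1400 | 25% | 25% | 28% |
| 0.7 | 0.2744 | 49% | 49% | 49% |

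The simulation used 4,000 trials per row. Adjusting both regressions for baseline outcome and baseline EEG, with an assumed baseline-to-week-4 correlation of 0.5 in each, leaves the shares at about 9%, 25% and 49%. Both paths are then significant in about 13%, 35% and 60% of trials. Baseline adjustment does not resolve direction.

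**The case against.** Several points on the other side are sound.

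- **The randomised EEG comparison is already in the plan.** A reader might infer that the article offers no valid EEG analysis. It does: Study Design names the effect of Tango on cognitive load as the endpoint, and Statistical analysis applies a mixed model to all outcomes, with baseline outcome among the fixed effects and a week-4 contrast as the primary estimand. It also plans Pearson correlations that include brain activity. What remains is the unqualified causal label.
- **EEG's role as mediator is partly inferred.** In Study Design the word for mediation attaches to the blood biomarkers. Background and rationale speaks of "potential physiological mediators of sensation and function among BC survivors" without naming EEG. The inference rests on the Statistical analysis sentence, which covers all of Aim 3, read with Objectives. If EEG was never meant as a mediator, that sentence should say so.
- **The visit pairing is not fixed.** An article may leave it to the analysis plan, and Objectives expects exploratory measures to change with 8 weeks of Tango. So it cannot be said that a reversed relation will be read as causal, only that it could be.
- **Later visits do give temporal order.** A reader might infer that no ordered pairing exists. That is too strong: crossover is optional, and marginal structural models can treat it as a time-varying exposure. What is lost is the unexposed randomised control.
- **The simulated sizes are built in.** EEG is made wholly a consequence of the outcome, the correlations are assumed, and the fitted model is a simple two-regression one, not a marginal structural model. The figures are not this trial's expected error.

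That only the two oddball conditions of the seven in Table 4 add a cognitive task is a separate matter and has no bearing on temporal order.

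**Conclusion.** The point holds in limited form. From the schedule alone, the direction between EEG change and change in symptoms or TUG-Cog cannot be identified within the randomised window, and no analysis plan can create an EEG visit before week 4. Lagged pairings restore order only by leaving the randomised Tango-versus-SOC comparison.

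The false share of 9% to 49% is a worst-case illustration under assumed correlations of 0.3 to 0.7 that the documents do not give. It shows that the error could be material, not how large it will be. Because Aim 3 is exploratory and the primary analyses are unaffected, severity is minor.

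**What to change.** In Statistical analysis, qualify the Aim 3 sentence for EEG:

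- State that the Aim 3 inference for cognitive load is the randomised, baseline-adjusted week-4 difference between arms. This is the effect Study Design already names, estimated with the mixed model already specified.
- Label any mediation result using week-4 EEG and week-4 outcomes as associational, and report the reverse-order model (outcome to EEG) beside it.
- Label any lagged analysis that uses visits after week 4 as non-randomised.

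This changes wording and adds one model; it needs no new data or visits. The downside is a weaker mechanistic claim. Enrolment is expected to run to December 2028 (Trial status), so the change can be made well before analysis.

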#### Repeated baseline schedule

Repeated baseline data have previously been collected and analyzed as described in Lantis et al., 2023 (46). Select measures (Tables 1 & 2, indicated with x^†^) are collected repeatedly prior to intervention to characterize within-subject variability (WSV) in CIN-related symptoms and function at baseline.

Similar to Lantis et al., 2023 (46), repeated baseline measures for postural control were achieved through collection of the postural control dynamics during silence (QEC) at the beginning of up to 3 visits, including the first screening test of postural control and 3–4 additional days.

